## Abstract

**Background:**

Survival after out-of-hospital cardiac arrest is closely linked to the quality of CPR, but in real life, resuscitation during prehospital care and ambulance transport is often suboptimal. Mechanical chest compression devices deliver consistent chest compressions, are not prone to fatigue and could potentially overcome some of the limitations of manual chest compression. However, there is no high-quality evidence that they improve clinical outcomes, or that they are cost effective. The Prehospital Randomised Assessment of a Mechanical Compression Device In Cardiac Arrest (PARAMEDIC) trial is a pragmatic cluster randomised study of the LUCAS-2 device in adult patients with non-traumatic out-of-hospital cardiac arrest.

**Methods/design:**

The primary objective of this trial is to evaluate the effect of chest compression using LUCAS-2 on mortality at 30 days post out-of-hospital cardiac arrest, compared with manual chest compression. Secondary objectives of the study are to evaluate the effects of LUCAS-2 on survival to 12 months, cognitive and quality of life outcomes and cost-effectiveness. Methods: Ambulance service vehicles will be randomised to either manual compression (control) or LUCAS arms. Adult patients in out-of-hospital cardiac arrest, attended by a trial vehicle will be eligible for inclusion. Patients with traumatic cardiac arrest or who are pregnant will be excluded. The trial will recruit approximately 4000 patients from England, Wales and Scotland. A waiver of initial consent has been approved by the Research Ethics Committees. Consent will be sought from survivors for participation in the follow-up phase.

**Conclusion:**

The trial will assess the clinical and cost effectiveness of the LUCAS-2 mechanical chest compression device. Trial Registration: The trial is registered on the International Standard Randomised Controlled Trial Number Registry (ISRCTN08233942).

## Background

Sudden cardiac death is a major cause of death and morbidity in the Western world. In Europe, approximately 700,000 people sustain a cardiac arrest in the community each year[1,2]. Resuscitation is attempted in about 45% of cases of which approximately 20% achieve a return of spontaneous circulation by the time of arrival at hospital and about 5% survive to hospital discharge[3,4]. Good quality cardiopulmonary resuscitation (CPR) has a significant impact on the likelihood of survival[5-7], yet it is difficult to perform in the prehospital environment due to the multiple tasks required upon arrival at a cardiac arrest. In addition, rescuer fatigue can reduce chest compression quality as early as 1 minute after commencing chest compressions[8].

The LUCAS-2 is a mechanical device that delivers sternal compressions at a constant rate of 100 per minute, to a fixed depth of 4 cm to 5 cm, using a piston with a suction cup attached that returns the chest to its normal expanded position. The rate and depth comply with International scientific guidelines on CPR[9]. It is easy to apply, stable in use, relatively light in weight (7.8 kg), and well adapted to use during patient movement on a stretcher and during ambulance transportation. The device is CE marked and has been on the market since 2002 in Europe. The device was originally gas-powered, a battery powered version (LUCAS-2) was introduced in 2009. Detailed descriptions of the device and experimental data from animal studies reporting increased cardiac output and cortical cerebral flow compared to manual standardised CPR have been published[10]. However there is a lack of robust evidence from human trials for the clinical and cost effectiveness of the device [11,12].

The Prehospital Randomised Assessment of a Mechanical Compression Device In Cardiac Arrest (PARAMEDIC) trial is a cluster randomised pragmatic trial of the clinical and cost effectiveness of the LUCAS-2 device versus manual chest compression, for adult patients in whom resuscitation is attempted following non-traumatic out-of-hospital cardiac arrest.

## Methods/Design

### Trial Approvals and Conduct

The trial is approved by the Coventry Research Ethics committee (for England and Wales) and Scotland A Research Ethics Committee. The trial is registered on the International Standard Randomised Controlled Trial Registry (ISRCTN08233942). It will be carried out in accordance with the Medical Research Council (MRC) Good Clinical Practice Guidelines[13], applicable UK legislation and the Standard Operating Procedures of the Warwick Clinical Trials Unit. The sponsor organisation for the trial is the University of Warwick. The trial is funded by the National Institute for Health Research (NIHR) Health Technology Assessment (HTA) Programme[14] and is a collaboration between the Universities of Warwick, Coventry, Leeds, Southampton and Surrey and the West Midlands, Scottish and Welsh NHS Ambulance Services. Further details can be found on the trial website[15].

The contribution of the manufacturers (JOLIFE AB) and distributors (Physio-Control UK) of the LUCAS-2 device will be limited to supply and servicing of LUCAS-2 devices, and training of study co-ordinating centre personnel. They will have no role in the design, conduct, analysis or reporting of the trial.

### Outcome Measures

The primary outcome for the trial is survival to 30 days post cardiac arrest. Secondary outcomes are: survival of event (sustained return of spontaneous circulation (ROSC) to arrival at hospital); survival to hospital discharge and to 12 months; health related quality of life at 3 and 12 months (measured by SF12 and EQ-5D); neurologically intact survival to 3 months (survival with Cerebral Performance Category (CPC) score 1 or 2); cognition at 12 months (Mini Mental State Examination (MMSE); anxiety and depression at 12 months (Hospital Anxiety and Depression Scale (HADS)); post traumatic stress at 12 months (PTSD civilian checklist (PCL-C)); hospital length of stay; intensive care length of stay.

### Eligibility Criteria

Vehicles that are in service at participating ambulance stations and may attend cardiac arrests will be included in the trial, and will randomised before recruitment starts to either the LUCAS or manual chest compression (control) arms. To maximise the efficiency of the trial, recruitment will be predominantly concentrated in urban areas.

Individual patients will be eligible if:

1. they are in cardiac arrest in the out-of-hospital environment on arrival of a trial vehicle;

2. the first ambulance resource to arrive is a trial vehicle

3. a resuscitation attempt is initiated by the attending paramedic, according to UK national guidelines;

4. the patient is known or believed to be aged 18 years or over.

Exclusion criteria will be:

1. traumatic cardiac arrest

2. known or clinically apparent pregnancy.

Treatment allocation of each individual participant will be determined by the first trial vehicle to arrive on scene. If this is a LUCAS trial vehicle, the patient will be included in the LUCAS arm, and if it is a control trial vehicle, the patient will be in the control arm. If a non-trial ambulance or rapid response vehicle arrives first and resuscitation is started, the patient will be excluded.

### Power and Sample Size

There are no national data on survival to 30 days post cardiac arrest. However, it is likely to be very similar to survival to hospital discharge, as most mortality will occur in the period immediately following a cardiac arrest. In a systematic review[1], the average survival to hospital discharge in 8 studies conducted in the UK was 8.1%. National audit data for England (2004-2006) indicate that the proportion of patients with ROSC at hospital admission is 14 to 16%[4]. Estimates of mortality in hospital vary from 50% to 70%, hence the incidence of survival to hospital discharge is expected to be between 4.5% and 8%[16]. A conservative estimate of survival to 30 days is therefore 5%.

No data currently exist from which a relevant intracluster correlation coefficient (ICC) can be calculated, and we have therefore assumed a conservative value of 0.01. The value of the ICC will be monitored at interim analyses by the Data Monitoring Committee (DMC), who will make recommendations for adjustments to the required sample size.

### Sample Size Required

We aim to detect, with 80% power, an increase in the incidence of survival to 30 days from 5% in the control arm to 7.5% in the LUCAS arm (a risk ratio of 1.5). The number of LUCAS clusters (vehicles) is limited by the number of devices available, but because control clusters (vehicles) do not require any specific equipment, we can include more control clusters than LUCAS clusters in the trial (see figure 1). Detection of the specified difference with a randomisation ratio of 1:2 and a cluster size of 15 requires 82 LUCAS and 163 control clusters (3675 participants in total). The primary outcome will be determined for close to 100% of trial participants, so there is no adjustment for losses of individual patients.

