#### Learning effects

Because LUCAS-2 will be new to paramedics in the areas where the trial is conducted, there is a possibility that there will be a learning effect, and its apparent effectiveness may increase through time as personnel become more familiar with its use. We will therefore allow a "run-in" period before the start of recruitment to the trial at each station. Participating vehicles will be randomised at the start of this period, LUCAS-2 will be used in the LUCAS arm, and trial data will be collected but will not be included in the main trial analysis.

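### The 3675 participants give 80% power only if every vehicle contributes exactly 15 patients; with no allowance for unequal vehicle sizes, the stated power is slightly too high

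*Protocol article*

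**What the plan says.** The section Sample Size Required sets the goal: "We aim to detect, with 80% power, an increase in the incidence of survival to 30 days", from 5% under manual compression to 7.5% under LUCAS-2. It then derives the size: "Detection of the specified difference with a randomisation ratio of 1:2 and a cluster size of 15 requires 82 LUCAS and 163 control clusters", which it totals as "3675 participants in total". The cluster size is a single number, and variation around it is not mentioned. The section Power and Sample Size assumes an ICC of 0.01. It has the Data Monitoring Committee (DMC) follow the ICC at interim analyses and advise on changes to the sample size.

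Two other places bear on how large each cluster becomes. Under Eligibility Criteria, "Vehicles that are in service at participating ambulance stations and may attend cardiac arrests will be included in the trial", and each patient belongs to the arm of the first trial vehicle on scene. Under Learning effects, a run-in takes place "before the start of recruitment to the trial at each station", so the start of recruitment is tied to the station.

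The abstract gives another total: "The trial will recruit approximately 4000 patients from England, Wales and Scotland". The text does not connect it with 3675.

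**The concern.** A vehicle's cluster size is the number of eligible arrests it reaches first. The trial does not set that number. The section Cluster design intends to include nearly all eligible patients, and no limit per vehicle is stated. Busy and quiet vehicles will therefore contribute different numbers, and even equally busy vehicles would differ by chance.

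When cluster sizes vary, the variance of the treatment comparison exceeds what the mean size implies, even if the ICC is exactly as assumed. A calculation with one fixed size then promises more power than the design has. The size in this protocol sits exactly at 80%, so it has no reserve to absorb the difference. What is at stake is the accuracy of the stated power, and whether the planned sample-size review would notice a shortfall. No estimate or test is affected.

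**Working it through.** **Inputs from the protocol article.** 30-day survival 5% against 7.5%, 80% power, 1:2 allocation, cluster size m = 15, and 82 + 163 = 245 clusters (Sample Size Required); ICC 0.01 (Power and Sample Size).

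**Assumptions.** Two-sided 5% significance is not stated for the sample size, but it fits the planned 95% confidence intervals and reproduces the stated total. The CV of vehicle size is not given; a range from 0.26 to 1.0 is used. The lower end is chance variation alone: 1/√15 = 0.26.

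**Step 1: reproduce the stated size.** Pooled-variance formula for two proportions, n being the LUCAS arm and 2n the control arm:

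n = [1.960 × √(1.5 × p̄(1 − p̄)) + 0.8416 × √(0.075 × 0.925 + 0.05 × 0.95/2)]² / 0.025²

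- p̄ = (0.075 + 2 × 0.05)/3 = 0.0583
- n = (0.5626 + 0.2568)² / 0.000625 = 1074.4
- Equal-cluster design effect: 1 + (15 − 1) × 0.01 = 1.14
- LUCAS: 1074.4 × 1.14 = 1224.8 patients, or 81.65 clusters of 15
- Control: 163.3 clusters
- Total: 3674 patients, against the stated 82, 163 and 3675

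The power of 82 × 15 = 1230 against 163 × 15 = 2445 patients is 80.1%. Three other settings do not give 3675: one-sided 2910, continuity-corrected 3878, and unpooled variance about 4000.

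**Step 2: allow for unequal clusters.** The design effect becomes 1 + [(1 + CV²) × m − 1] × ICC. At CV 0.5, for example, it is 1 + [1.25 × 15 − 1] × 0.01 = 1.178. Power is then computed with both arms divided by the design effect. The total needed for 80% is 3 × 1074.4 × design effect, reached by adding vehicles of mean size 15.

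| CV (assumed) | Design effect | Power at 3675 | Total for 80% |
|---|---|---|---|
| 0 | 1.140 | 80.1% | 3674 |
| 0.26 | 1.150 | 79.7% | 3707 |
| 0.5 | 1.178 | 78.9% | 3795 |
| 0.7 | 1.214 | 77.7% | 3911 |
| 1.0 | 1.290 | 75.3% | 4158 |

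An approximation for an analysis that weights clusters efficiently gives nearly the same power: 79.0%, 77.9% and 75.4% at CV 0.5, 0.7 and 1.0.

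**Step 3: the abstract's 4000.** The number of LUCAS vehicles is limited by the devices available, so the cautious case keeps the same 245 vehicles. The mean size is then 4000/245 = 16.3.

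| CV (assumed) | Design effect at m = 16.3 | Power at 4000 |
|---|---|---|
| 0.5 | 1.194 | 81.5% |
| 0.7 | 1.233 | 80.3% |
| 0.8 | 1.258 | 79.6% |
| 1.0 | 1.316 | 77.8% |

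With 4000 patients, 80% therefore holds up to a CV of about 0.7. If the extra patients came from added vehicles of mean size 15, it would hold up to about 0.8 (80.2%).

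**The case against.** The case on the other side is substantial.

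- **The arithmetic is right.** 3675 follows from the stated inputs. A reader might infer a miscalculation, or conclude that the trial has 75% power. The document supports neither. The 75% needs a CV of 1.0, for which it offers no evidence, and chance variation alone costs less than half a point.
- **Other inputs matter as much.** The protocol calls its ICC and its control rate conservative. As an illustration only, an ICC of 0.005 gives 81.8%, 81.2% and 79.9% at CV 0.5, 0.7 and 1.0. A control rate of 6% with the same risk ratio gives 82.7% even at CV 1.0. The reverse also applies: 4.5%, the low end of the protocol's expected range, gives 74.5% at CV 0.5. This keeps the point small. It does not remove it, because the 80% is claimed at 5% and 0.01.
- **A sample-size review is planned.** It is tied to the ICC. Variable cluster size raises the variance even when the ICC equals 0.01, so a report that the ICC is as assumed would miss it.
- **4000 exceeds 3675.** A reader might infer two conflicting sample sizes, or doubt about which total ends recruitment. The document does not support this: one figure is what detection requires, the other what the trial expects to recruit, and neither is called a closing rule. Nor can 4000 be read as a deliberate allowance for unequal clusters, or as the result of the unpooled formula to which it happens to be close, because no derivation is given.
- **A journal article condenses.** The full protocol may hold a CV. Even so, the figures printed here match a calculation without one.

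**Conclusion.** The point holds as a minor one. The 82 and 163 clusters and the 3675 participants are correct if all vehicles contribute 15 patients each. The design does not produce that, so 80% at 3675 is slightly overstated. With 5% against 7.5%, ICC 0.01 and a two-sided 5% test, the loss against 80.1% is about 0.3 points for chance variation alone, 1.2 points at CV 0.5, 2.4 at 0.7 and 4.8 at 1.0. Which of these applies cannot be told from the document. The abstract's 4000 is unreconciled with 3675, not in conflict with it, and would restore 80% up to a CV of about 0.7 in the same 245 vehicles.

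**What to change.** 1. In Sample Size Required, replace the implied factor of 1.14 by 1 + [(1 + CV²) × m − 1] × ICC, and state the CV assumed.
2. Then do one of two things. Either keep 3675 and restate its power over the CV range (78.9% at 0.5, 77.7% at 0.7, 75.3% at 1.0), or name the abstract's 4000 as the target in this section and claim 80% only for a CV up to about 0.7.
3. In Power and Sample Size, have the DMC's review use the whole design effect, with the observed variation in patients per vehicle as well as the ICC.

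The cost is one paragraph of text and one extra quantity in the interim report, which can be counted from data already collected. The drawback is a slightly less favourable stated power if 3675 is kept. If 4000 is named, the recruitment figure already in the abstract becomes the target.

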**Figure 1 F1:**
[figure not shown]
**Flow chart for PARAMEDIC Trial**.

### Consent

Prospective consent from research participants prior to enrolment is impossible in this trial; the occurrence of an out-of-hospital cardiac arrest is unpredictable, and a victim becomes unconscious within seconds. Treatment (in the form of CPR) must be started immediately in an attempt to save the person's life. It is therefore not practical to consult a carer or independent clinician without causing the potential participant harm as a result of delaying treatment. Conducting research in emergency situations where a patient lacks capacity is regulated by the Mental Capacity Act (2005) in England and Wales and the Adults with Incapacity Act (2000) in Scotland. The relevant ethics committees have determined that the research methods are compliant with the requirements of this legislation.

Consent for follow-up will be sought from all participants who survive to hospital discharge. If a participant lacks capacity to give informed consent we will seek the views of a personal consultee in order to establish the patient's wishes.

### Protection against Bias

#### Cluster design

Selection bias is a major potential problem in cluster randomised trials: patients with different characteristics may be recruited to the two trial arms[17]. Further bias can arise where a large proportion of eligible patients are not included in the trial, as the probability of inclusion may be related to the intervention. In this trial we will identify eligible patients from routinely collected ambulance service data, which will allow us to identify and include close to 100% of the eligible patients, thus avoiding selection bias.

#### Threshold for resuscitation

Paramedics need to make a rapid decision as to whether to resuscitate someone in cardiac arrest upon arrival at the scene. It is possible that application of the Recognition of Life Extinct (ROLE) criteria[18] will differ between the trial arms. If paramedics believe strongly that LUCAS-2 is effective, some of them may attempt to resuscitate patients in the LUCAS arm who have no chance of survival, and for whom a resuscitation attempt would not normally be considered. This would result in a group of patients with very low probability of survival being recruited to the LUCAS arm but not the control arm, potentially masking any beneficial effect of LUCAS-2.

We will monitor the accumulating trial data for evidence of a between-group difference in threshold as follows: (1) proportion of arrests where resuscitation attempted versus cardiac arrests attended (2) patient age profile (3) proportion receiving bystander CPR (4) time from collapse to trial vehicle arrival and (5) proportion of patients in asystole. If evidence of bias is detected corrective action will be taken.

#### Compliance

Compliance (whether LUCAS-2 was used for all eligible patients in the LUCAS-2 arm and none in the control arm) will be monitored by review of ECG recordings taken during resuscitation. Recorded compression waveforms will be analysed to determine whether LUCAS-2 was used and to confirm the presenting rhythm and duration of resuscitation.

#### Learning effects

Because LUCAS-2 will be new to paramedics in the areas where the trial is conducted, there is a possibility that there will be a learning effect, and its apparent effectiveness may increase through time as personnel become more familiar with its use. We will therefore allow a "run-in" period before the start of recruitment to the trial at each station. Participating vehicles will be randomised at the start of this period, LUCAS-2 will be used in the LUCAS arm, and trial data will be collected but will not be included in the main trial analysis.

#### Crew preferences

With randomisation by vehicle, a potential source of bias is that paramedics who are motivated to use LUCAS-2 will select LUCAS vehicles, whilst those who dislike the device may avoid it. In order to check for this possibility, we will review records of crews members present at each cardiac arrest to check individuals who consistently appear in one arm. If swapping between LUCAS and control trial vehicles is found to occur, the staff involved will be given extra training in the trial procedures.

#### Blinding

Because of the nature of the interventions, paramedics cannot be blinded, and will be aware of treatment allocations. Control room personnel will be blinded to the allocation of the ambulance service vehicles, to ensure that there is no bias in whether a LUCAS or control trial vehicle is sent to an incident that is likely to be a cardiac arrest. Patients themselves will be unaware of their treatment allocation at the time of the intervention, though they may subsequently be unblinded by relatives or friends who are aware that LUCAS-2 was used. To ensure blinding of outcome assessment as far as possible, research nurses assessing patients at follow-up visits will be blinded to the allocated treatment group.

### Trial Intervention/Treatments

#### LUCAS arm

The trial will use the LUCAS-2 device, (JOLIFE AB, [name]).

The LUCAS arm will receive resuscitation according to the Resuscitation Council (UK)[19] and Joint Royal College Ambulance Liaison Committee (JRCALC) advanced life support guidelines[20] with the exception that the LUCAS-2 device will be deployed to replace manual chest compressions (see figures 2 and 3). All standard advanced life support interventions will be provided including drug administration, defibrillation and advanced airway management as required.

**Figure 2 F2:**
[figure not shown]
**Treatment algorithm for control arm**.

**Figure 3 F3:**
[figure not shown]
**Treatment algorithm for LUCAS arm**.

On arrival, two minutes of LUCAS-2 CPR (5 cycles of 30:2) will be administered before a countershock if the patient is in ventricular fibrillation (VF) or pulseless ventricular tachycardia (VT). Operational experience shows that LUCAS-2 can be positioned and activated within 20 to 30 seconds of arrival at the patient. Prior to intubation, compressions will be provided using the 30 compressions to 2 ventilation mode. If the patient is intubated, asynchronous compressions and ventilations will be provided, with a ventilation rate of 10 per minute. A bag-valve device will be used to manually provide ventilations.

Defibrillation will be performed using the following sequence: stop LUCAS-2 device, analyse heart rhythm; if shock indicated, restart LUCAS-2, charge, deliver shock, continue CPR for 2 minutes. This will minimize deleterious pre and post shock pauses in compressions. The LUCAS-2 device will be used in place of standard chest compressions as long as continued resuscitation is indicated, including outside the ambulance and during transport to hospital. The trial intervention will cease after care is handed over to the medical team at hospital.

If a patient in the LUCAS arm arrives at hospital with the LUCAS-2 device running, the device should be removed and resuscitation should continue with manual compressions. Hospitals will be given information about the trial prior to the start of recruitment.

